**Fig. 2 Fig2:**
[figure not shown]
Flow diagram of Poriborton and Poriborton-Extension

Our field implementation team is trained in technical issues for gas stove installation, troubleshooting and maintenance, and cylinder replacement. They will continue to provide support to intervention households who require external assistance as necessary. These stoves will adhere to the Bangladesh Standards and Testing Institution requirements. We will replace the stoves in case of mechanical faults during the 2 years of use. Control women will continue with usual cooking practices (mostly traditional cooking) and will be followed up for outcome evaluation up to 24 months of child’s age. Participants from the control arm will be provided 200 Taka as time compensation during the six visits (3, 6, 12, 18, 24 months of child’s age).

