#### Sample size {14}

We expect the final sample size to be at least 1854 children (927 in each arm) with follow-up up to 24 months of child’s age available for analysis. This assumes ten per cent loss-to-follow-up due to mortality in the first 2 years of age (3%), migration out (3%), and withdrawals (2%). For this sample size, we have at least 88% power to detect a 20% lower risk (relative risk =0.8) in stunting, assuming 35% stunting in the control vs 28% in the intervention, an intraclass cluster correlation of 0.02, which is based on the previous cRCT on stunting, [26] and a two-sided significance level of 0.05. If the intraclass correlation is twice as large, i.e., intraclass correlation 0.04, [25], we would still have 80% power. For the secondary outcomes, the final sample size will provide at least 80% power to detect moderate effect sizes for many, if not all, secondary outcomes. For example, we will have 90% power to detect a standardized difference of 0.2 between arms for height-for-age *z*-score. Any differences in perinatal outcomes from Poriborton will not impact the integrity of the extension. We expect reduced perinatal mortality and higher birth weights. Additional live births will result in a slightly higher sample size in the intervention arm for the extension. We investigated this scenario in our power calculation and found the differences in cluster size will remain relatively small and less likely to impact the power.

For the personal exposure of household air pollution, a sample size of 120 children from each arm will be used to estimate reductions in PM2.5. This sample size will allow us to detect a 28% difference (50% and 70% in intervention and control, respectively) (WHO target [3]) with > 80% power.

The expected number of live births (> 7 days old) eligible is 2154, corresponding to all women enrolled in Poriborton from October 2020, of which we expect 10% fetal loss and up to 5% lost-to-follow-up due to migration (3%) or withdrawal (2%). Of the 2154 births (infants), we expect 2060 to be enrolled into the Poriborton-Extension, conservatively assuming that 4% of the newborns die prior to enrollment or decline to participate in the extension.

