#### Implementation {16c}

An independent statistician will generate the allocation sequence. All participants in the intervention clusters will continue receiving the intervention from the original Poriborton trial, and all participants in the control arm continue their usual cooking practice and do not receive any intervention. To minimize bias, since participant blinding is not possible, we have separate intervention and evaluation staff. Trial evaluators will be blinded to the hypothesis, and we will conduct our analysis blinded to the treatment arms.

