##### Process evaluation

We will collect mixed-methods data to assess protocol adherence, LPG continued and exclusive and correct use, community engagement, awareness and knowledge of benefits and correct usage of LPG, and contextual factors for adherence and non-adherence of exclusive and continuous use of LPG. Data will be collected at regular time points using quantitative (regular project monitoring records/data) and qualitative methods (interviews and focus groups of a sub-sample of women and household members, and through direct observation). This data will assist with understanding adherence to the intervention (intensity of the intervention) and barriers and facilitators to clean cooking adoption, which will assist with identifying contextual factors influencing the trial outcomes, interpreting our trial findings, and also provide insight for replicating and scale-up.

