### Plans to promote participant retention and complete follow-up {18b}

Our intervention is a high-value intervention and is itself a method to promote participant retention and complete follow-up. As this is an extension of the original trial we already know that participants are willing to continue with the intervention. Participants in the control arm receive small gifts (child blankets, toys and transport costs reimbursed) to promote retention and complete follow-up. Data will not be collected from those who discontinue with the intervention.

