### Statistical methods

#### Statistical methods for primary and secondary outcomes {20a}

The main analyses will be by intention to treat. Analyses will be conducted at the infant level but will be adjusted for the cluster randomization using a random effect for clusters in all model development [43]. We will use linear models for continuous outcomes (e.g., height-for-age *Z*-scores) and logistic models for binary outcomes. Bayley developmental scores will be used mostly as continuous variables after converting into both composite scores from conversion tables and *Z*-scores using the mean and standard deviation of control group children across age bands. Functional capacity index and behavior scores will be summed up and compared between arms. Models will include treatment group as a fixed effect and a random effect for the cluster randomization. For data where we have repeated measurements will also include time as a fixed effect and infants as a random effect to account for repeated measurements (three-level mixed models). The balance of household characteristics will be assessed between arms, and secondary analyses will be conducted, adjusting for any imbalanced characteristics. We will use Stata for all analyses.

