#### Methods in analysis to handle protocol non-adherence and any statistical methods to handle missing data {20c}

We will do a complete case analysis and to avoid biasing the results or excluding data we will apply missing value imputation and undertake sensitivity analysis.

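### The rule that stops data collection when a household discontinues LPG conflicts with intention to treat and creates a loss in the LPG arm only

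*Protocol article*

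**What the plan says.** Four statements in the protocol article bear on this.

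- Retention and complete follow-up {18b}: "Data will not be collected from those who discontinue with the intervention". The sentence carries no qualification.
- Statistical methods {20a}: "The main analyses will be by intention to treat".
- Implementation {16c}: "all participants in the control arm continue their usual cooking practice and do not receive any intervention". The text after Fig. 2 adds that control women "will be followed up for outcome evaluation up to 24 months of" the child's age, with no condition about fuel use.
- Non-adherence and missing data {20c}: "We will do a complete case analysis and to avoid biasing the results or excluding data we will apply missing value imputation", together with a sensitivity analysis. Neither the imputation model nor the sensitivity analysis is described.

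The sample size section {14} allows 10% loss and names death (3%), migration (3%) and withdrawal (2%) as its causes. Stopping LPG is not named. No section says that outcome visits continue after a household stops LPG.

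**The concern.** Intention to treat needs the outcome to be sought from every enrolled child in the arm to which the cluster was randomised, whatever the household did afterwards. The retention rule makes measurement depend on behaviour after randomisation, and that behaviour can occur in one arm only.

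Households that give up free LPG may differ from those that keep it in wealth, cooking habits or the health of the child. If they do, leaving their children unmeasured shifts the stunting prevalence in the LPG arm and leaves the control arm as it is. The primary outcome, stunting at 24 months, is directly exposed to this, and so are the 24-month Bayley scores. An analysis plan cannot repair it afterwards, because the measurements would never have been taken.

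**Working it through.** **Step 1. Can the rule apply to both arms?** Control households receive no intervention {16c}, so they have nothing to discontinue, and they are followed to 24 months. The rule can remove children from the LPG arm only. Death, migration and withdrawal remain possible in both arms.

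**Step 2. Whom does it remove?** It removes those who discontinue. The process evaluation plans data on "contextual factors for adherence and non-adherence of exclusive and continuous use of LPG", so households with partial or mixed fuel use are expected in the study and stay in it.

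**Step 3. The plan's own figures.** Inputs from {14} and {16a}: 927 children and 103 clusters per arm (927/103 = 9 per cluster), ICC 0.02, 35% versus 28% stunting, two-sided 5% level.

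- Design effect: 1 + (9 − 1) × 0.02 = 1.16. Effective number per arm: 927/1.16 = 799.
- Power by the normal approximation: 85.4%. The article states at least 88%, which I do not reproduce at 927 per arm.
- At ICC 0.04 I obtain 80.7%, which agrees with the stated 80%. The 88% is a separate matter, and nothing below depends on it.

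**Step 4. Power cost of the rule.** Discontinuation rates are assumed. The loss is taken from the LPG arm only, with control kept at 927 and ICC 0.02.

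| Assumed discontinuation | Power |
|---|---|
| 0% | 85.4% |
| 2% | 85.1% |
| 5% | 84.7% |
| 10% | 83.8% |
| 20% | 81.7% |

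**Step 5. Bias with no true effect.** Let q be the fraction of LPG children who are dropped and s the stunting prevalence among them. Both are assumptions. True prevalence is 35% in both arms.

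- Observed LPG prevalence: p = (0.35 − q × s)/(1 − q).
- LPG number: n = 927 × (1 − q), with design effect DE = 1 + (n/103 − 1) × 0.02.
- SE = √[0.35 × 0.65 × 1.16/927 + p(1 − p) × DE/n].
- Type I error = Φ(−1.96 + d/SE) + Φ(−1.96 − d/SE), where d = 0.35 − p.

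Example with q = 10% and s = 50%:

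- p = (0.35 − 0.05)/0.90 = 0.333 and d = 0.0167.
- n = 834.3 and DE = 1 + 7.1 × 0.02 = 1.142.
- SE = 0.0243 and d/SE = 0.687.
- Type I error = 10.6%.

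| q | s | LPG arm observed | Relative risk | Type I error |
|---|---|---|---|---|
| 2% | 50% | 34.7% | 0.99 | 5.2% |
| 5% | 50% | 34.2% | 0.98 | 6.2% |
| 10% | 40% | 34.4% | 0.98 | 5.6% |
| 10% | 50% | 33.3% | 0.95 | 10.6% |
| 15% | 50% | 32.4% | 0.92 | 19.1% |
| 15% | 28% | 36.2% | 1.04 | 7.9% |

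**Step 6. Bias with the planned effect (true relative risk 0.80).** The same formula with 0.28 in place of 0.35 gives 0.79 for 2% discontinuing with 45% stunted. For 15% discontinuing with 40% to 45% stunted it gives 0.74 to 0.71.

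These are complete-case results. Imputation would change them by an amount that depends on its assumption.

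**The case against.** **The sentence may mean leaving the study.** It follows a remark that participants are known to be willing to go on with the intervention, in a paragraph about staying in the trial, and participants have a right to withdraw. This reading is possible but strained. The words refer to the intervention, and {14} already lists withdrawals as a separate cause of loss. If consent withdrawal was meant, the wording still invites field staff to apply it literally, and the same edit cures it.

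**Imputation keeps the children in the analysis.** In part it does. Nothing says that data collected before discontinuation are discarded. Table 1 schedules length at birth, 7–10 days and 3, 6, 12 and 18 months, and {20a} plans mixed models for repeated measurements. A child dropped late has a growth history. A reader might infer that intention to treat becomes impossible, but the document does not support that. What is lost is intention to treat on observed outcomes. No outcomes after discontinuation would exist to show whether growth then follows the imputed path.

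**Discontinuation may be rare.** LPG is free to 24 months, with household visits every 2 months. The only voluntary exit rate in the article is the 2% for withdrawals. The named losses sum to 8% against the stated 10%, so two points are unassigned. All of this stands, and at 2% the bias is slight.

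**The contrast is not on-treatment against all-comers.** A reader might infer this, but partial users remain in the LPG arm, and the control arm also loses children to death, migration and withdrawal.

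**Conclusion.** The conflict between {18b} and {20a} is plain in the text, and no other section resolves it. Because the article states a field rule, this is not a detail left to the full protocol or the analysis plan.

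The size of the harm is not known. Over the assumed cases with no true effect, the relative risk runs from 0.92 to 1.04 and the type I error from 5.2% to 19.1%. Material inflation needs both a substantial discontinuation rate and a large difference in stunting between those who stop and those who continue. The 10.6% and 19.1% figures require 10% to 15% discontinuing with half of those children stunted. A reader might take them as the expected error rate, but the article gives no basis for those inputs. The direction is also open: discontinuers who are better off would make LPG look harmful.

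Loss of power is not the issue. The issue is a one-sided loss on the primary outcome, created by the protocol itself, that cannot be undone once the 24-month measurement is missed. Confidence is high on the contradiction and low on the magnitude. It should be corrected.

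**What to change.** Replace the sentence in {18b} with wording such as: Households that stop or reduce LPG use remain in follow-up; all scheduled outcome assessments, including 24-month anthropometry and Bayley, continue unless the caregiver withdraws consent to follow-up.

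In addition:

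- Record LPG discontinuation separately from withdrawal from follow-up, with dates.
- Analyse every enrolled child in the arm to which the cluster was randomised.
- For any child already dropped because the household stopped LPG, try to obtain the 24-month length, with the caregiver's consent.
- Report how many children were lost in this way.

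The change concerns data collection only. It costs one protocol sentence, an instruction to field staff and a few extra visits by the evaluation team that is already in place.

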### Data management {19}

All electronic data is stored on a password secured server backed-up at icddr,b, that only limited staff can access. Data will be stored for 15 years as per trial sponsor funding rules. We will adhere to good data management practices, including collection, validation, and training. Our data will be publicly available as per international standards after 15 years of the trial completion.

### Confidentiality {27}

We have gate-keeper consent from community leaders and relevant government officials. All women and or their guardians provide informed consent to participate and have the right to withdraw at any stage without penalty or loss. The investigators will ensure the privacy, anonymity, and confidentiality of the information provided by respondents and will store all trial information in an encrypted database with all identifiers removed.

### Plans for collection, laboratory evaluation, and storage of biological specimens for genetic or molecular analysis in this trial/future use {33}

N/A as this trial does not collect biological specimens.

### Statistical methods

#### Statistical methods for primary and secondary outcomes {20a}

The main analyses will be by intention to treat. Analyses will be conducted at the infant level but will be adjusted for the cluster randomization using a random effect for clusters in all model development [43]. We will use linear models for continuous outcomes (e.g., height-for-age *Z*-scores) and logistic models for binary outcomes. Bayley developmental scores will be used mostly as continuous variables after converting into both composite scores from conversion tables and *Z*-scores using the mean and standard deviation of control group children across age bands. Functional capacity index and behavior scores will be summed up and compared between arms. Models will include treatment group as a fixed effect and a random effect for the cluster randomization. For data where we have repeated measurements will also include time as a fixed effect and infants as a random effect to account for repeated measurements (three-level mixed models). The balance of household characteristics will be assessed between arms, and secondary analyses will be conducted, adjusting for any imbalanced characteristics. We will use Stata for all analyses.

#### Interim analyses {21b}

N/A as based on previous trial we anticipate minimal risk to participants.

#### Methods for additional analyses (e.g., subgroup analyses) {20b}

In the PM2.5 sub-sample, we will analyze the association of household air pollution (measured by PM2.5) by replacing treatment group with log (PM2.5): PM2.5 will be examined as a continuous exposure variable, but a secondary analysis will also examine the effect of exposure where the PM2.5 exposure variable is categorized by the WHO critical value. We will use Stata for all analyses.

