Over 149 million children under five suffered from stunting in 2020 [6], and HAP is considered to account for a large proportion of stunting [7, 8]. Stunting is defined as height-for-age 2 standard deviations below the growth standards, and stunted children have both physical and cognitive developmental delays. Few studies examine the biological pathways by which HAP causes stunting [9]. It may be through the same pathway that exposure to environmental tobacco smoke reduces birth weight, thus contributing to stunting [10, 11], or through acute respiratory infections [12], or anemia [13], all of which are associated with stunting. During the antenatal period, exposure to air pollution may induce oxidative stress or systematic inflammation that occurs, as a result, may be a pathway to growth retardation [9]. Exposure to air pollution during the postnatal period may promote stunting via impairments in the immune system and development, clinical and subclinical infections, changes in nutrition (dietary intake and metabolism), and altered bone metabolism [9]. The epidemiological evidence is from retrospective observational studies. A recent review of solid fuel use on stunting ascertained that those children living in homes that used solid fuels as the primary fuel source were three times more likely to be severely stunted compared to those in households using cleaner fuel, such as liquefied petroleum gas (LPG) [12]. In a population-based study in India, children exposed to solid fuel compared to those unexposed had differences in mean height-for-age *z*-scores of 0.61, a 21.3% difference after accounting for confounding [14]. Further research from India revealed households using clean cooking fuels had reduced the likelihood of stunting after controlling for socioeconomic and demographic factors [8]. However, there have been no randomized controlled trials of HAP interventions and stunting, which this study aims to address.

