##### HAP exposure

We will measure personal HAP exposure in two ways: using our (1) structured questionnaires used in Poriborton [38], which include smoking in the home, and other known household air pollution variables, and (2) particulate matter: continuous by nephelometry and time-averaged filter-based measurements of particulate matter PM2.5 concentrations. Also, time-averaged black carbon, brown carbon, and tobacco smoke mass concentrations from the filter [39]. The Enhanced Children’s MicroPEM (ECM) is designed specifically for children aged less than 5 years. For children who are not mobile and are carried by their mother, the ECM will be carried by mothers. Once the children are mobile, the device will be worn by the child. [name] and his team have used this successfully and safely in South Africa and Malawi. It weighs ~ 150 g and is worn in a culturally appropriate pouch (that we developed) and collected at 6, 12–16 months, and 24 months of age.

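### The additional PM2.5 analysis puts a non-randomised exposure in place of the randomised arm, and the plan's only adjustment rule does not target confounders of PM2.5

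*Protocol article*

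**What the plan says.** The exposure analysis is defined in the protocol article under Methods for additional analyses {20b}, by a single change to the trial model: "we will analyze the association of household air pollution (measured by PM2.5) by replacing treatment group with log (PM2.5"). A categorised form follows: "a secondary analysis will also examine the effect of exposure where the PM2.5 exposure variable is categorized by the WHO critical value".

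The model being changed is in Statistical methods for primary and secondary outcomes {20a}: "Models will include treatment group as a fixed effect and a random effect for the cluster randomization". For repeated measurements it "will also include time as a fixed effect and infants as a random effect to account for repeated measurements (three-level mixed models").

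The same section contains the plan's only covariate rule: "The balance of household characteristics will be assessed between arms, and secondary analyses will be conducted, adjusting for any imbalanced characteristics".

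Sample size {14} sets the size of the sub-sample: "a sample size of 120 children from each arm will be used to estimate reductions in PM2.5".

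Two other places bear on confounding. Background and rationale {6a} cites Indian evidence that clean-fuel households had "reduced the likelihood of stunting after controlling for socioeconomic and demographic factors". HAP exposure describes questionnaires "which include smoking in the home, and other known household air pollution variables".

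**The concern.** The main model can do without covariates because arm was randomised. Once arm is taken out and measured PM2.5 put in, that justification is gone. PM2.5 can differ between households within the same arm for reasons connected to their means and living conditions, and those conditions can also affect growth. The article accepts this in principle, since its background relies on evidence adjusted for socioeconomic factors.

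The adjustment rule in {20a} does not close the gap. It is triggered by imbalance between arms, whereas confounding of PM2.5 depends on association with PM2.5 and with the outcome. A factor spread perfectly evenly over the two arms can still confound. The cluster random effect does not remove differences between households within a cluster.

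At stake is the reading of a secondary result. A coefficient for PM2.5 could be statistically significant with no effect of PM2.5 behind it.

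**Working it through.** **1. The plan's own figure for the sub-sample.** Sample size {14} gives 120 children per arm, 50% versus 70%, and power above 80%. The two-sided 5% level is stated for the primary outcome and assumed to apply here. Ignoring clustering:

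z = [0.20 × √120 − 1.96 × √(2 × 0.6 × 0.4)] / √(0.7 × 0.3 + 0.5 × 0.5) = (2.191 − 1.358) / 0.678 = 1.23, so power is 89%.

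The stated figure is reproduced, and 20/70 = 28.6% matches the stated relative difference. It concerns the comparison of arms. The article states no power or error rate for the exposure-response model.

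**2. The model after substitution.** Start with arm, cluster, and time and infant where measures repeat. Replace arm by log(PM2.5). What remains is log(PM2.5), cluster, time and infant, with no household or socioeconomic term.

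**3. Size of the problem, by arithmetic.** Assume that PM2.5 has no effect. Let one socioeconomic factor correlate r₁ with log PM2.5 within arm (in the direction of lower exposure) and r₂ with the growth score. With no shift in PM2.5 between arms, the spurious correlation has size r₁ × r₂. With N = 240, the Fisher approximation gives a test statistic centred at atanh(r₁r₂) × √237, and the false-positive rate is the chance that it exceeds 1.96 in absolute value.

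- r₁ = r₂ = 0.2: spurious correlation 0.04, centre 0.62, rate about 9%.
- r₁ = r₂ = 0.3: spurious correlation 0.09, centre 1.39, rate about 28%.
- r₁ = r₂ = 0.4: spurious correlation 0.16, centre 2.48, rate about 70%.

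**4. Check by simulation.** 2000 runs per setting, 120 children per arm, true effect zero, ordinary least squares, nominal 5%. The arm shift in log PM2.5, in within-arm SDs, is also an assumption.

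| r₁ = r₂ | No arm shift | Shift 0.5 SD | Shift 1.0 SD |
|---|---|---|---|
| 0.2 | 9% | 10% | 9% |
| 0.3 | 30% | 27% | 23% |
| 0.4 | 70% | 68% | 60% |

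Unequal correlations between 0.2 and 0.4 were also run. Over all settings the spurious slope was about −0.03 to −0.16 outcome SD per SD of log PM2.5. With the factor in the model, the false-positive rate was 4.3% to 6.1%. The comparison by randomised arm in the same data stayed at 3.8% to 6.0%.

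**5. Effect of measurement error.** A separate simulation with a 0.5 SD arm shift and exposure reliability of 0.5 gave 7%, 16% and 41% for correlations of 0.2, 0.3 and 0.4. Noisy exposure measurement lowers the rate but does not bring it back to 5%.

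**The case against.** The strongest objection is that this is a short description, in a condensed article, of an additional analysis. No sentence says that the model will be unadjusted, and a covariate list is commonly left to the SAP, which is not shown. A reader might infer that the plan rules out confounders; the text does not support that. What stands is narrower. The article does fix the model by substitution, and the one adjustment rule it states has the wrong trigger for this analysis. The secondary adjusted analyses in {20a} show that adjustment is part of the plan, but not that it would capture confounders of PM2.5.

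A second objection concerns purpose. A reader might infer that this analysis is meant to show that lower PM2.5 is why children grow better, or that it will be given the standing of the randomised comparison. The article says neither: it places the analysis among additional ones and calls its target an association. It does, however, use the word effect for the categorised form.

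Third, the magnitude rests on assumed correlations, and the simulation omitted the cluster and infant random effects. Both points are correct. The figures show what could happen, not what will.

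Fourth, adjusting for everything collected could do harm. Food security is measured at 3, 12 and 24 months, after the intervention began in pregnancy, and household income/expenditure is a trial outcome, so both may be changed by free fuel. Home smoking is itself a source of PM2.5. This objection stands in full and shapes the fix.

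**Conclusion.** The concern holds for the additional PM2.5 analysis only. As written, the PM2.5 coefficient is an observational quantity from a model with no household confounders, and the between-arm balance rule does not supply them. That conclusion follows from the text. Its size does not: the range of roughly 10% to 70% against a nominal 5% depends on the assumption that one socioeconomic factor correlates 0.2 to 0.4 with both PM2.5 and growth, and the lower end is a modest inflation. A reader might take the upper end as the expected error rate, but the documents give no correlation and no measurement reliability that would support this.

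The primary outcome and the other intention-to-treat comparisons by arm are not affected. The point is worth correcting because the remedy is cheap.

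**What to change.** In {20b}, specify the exposure-response model with its own covariates, fixed in advance and chosen regardless of balance between arms:

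- household and socioeconomic characteristics measured before the intervention, drawn from those the plan already intends to compare between arms;
- child age (partly covered by the time term where measures repeat), season of sampling, and whether the mother or the child wore the monitor.

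Keep variables that the intervention may change, such as food security and household income/expenditure, out of the main exposure model. Add home smoking only in a sensitivity analysis, because it is also a source of the exposure being studied. Describe both the continuous result and the result by WHO category as observational associations, not effects.

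The cost is a few degrees of freedom in a sub-sample of 240 children. Residual confounding by unmeasured or poorly measured factors remains possible and should be acknowledged when the result is reported.
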